## Abstract

**Background: **New approaches are required to slow down or reverse increasing trends of levels of delta-9-tetrahydrocannabinol (THC) and cannabis-attributable hospitalizations in Germany. Legal access to cannabis may constitute one viable effective policy response; however, available evidence does not suffice to inform a regulation model for Germany. The proposed study aims to reduce harm for cannabis users through legal access to herbal cannabis through pharmacies.

**Protocol:** A quasi-experimental study comparing cannabis users with legal access to herbal cannabis (Berlin, intervention group) to those without legal access (Hamburg, control group) (total N=698). As the primary outcome, we hypothesize that: 1) illegal THC consumption will reduce by at least 50% in the intervention group and 2) total THC exposure in the intervention group will be reduced by at least 10% lower than that of the control group, taking into account baseline values. Secondary outcomes comprise measures of frequency of use, THC-impaired driving, and mode of administration. Paired t-tests and multilevel regression models will be performed for statistical analyses.

**Discussion: **This study proposal is currently being reviewed by the ‘Federal Institute for Drugs and Medical Devices’ – the body responsible for approving research studies on classified substances, including cannabis. Upon approval and prior to the start of the study, a full ethical review will be undertaken. Results may inform a regulation model for Germany and other jurisdictions and are expected to deepen the understanding of the effects of legal access to cannabis.

**Pre-registration: **German Clinical Trials Register (DRKS), DRKS00020829

## Introduction

Cannabis remains the most prevalent illegal drug in Europe and other regions worldwide
^1^. In the EU, 14.4% of people aged 15–34 years indicated past-year use of cannabis
^2^. In the past decade, several trends adverse to public health have been observed, including rising prevalence of cannabis use, growing treatment demand for cannabis problems
^3^, and increases in potency levels in both herbal cannabis and resin
^4^. These trends are also mirrored in Germany, where, since 2006, prevalence of past-year use increased by 75%
^5^, treatment demand increased by 113%, and potency of resin increased by 119% (data for herbal cannabis not available
^6^). Moreover, the number of cannabis-related offences has risen by 38% in the same period
^7^.

To date, effective policy responses to the above-outlined trends could not be observed. In fact, these trends demonstrate that current cannabis policies in Germany have not resulted in reductions in drug demand. Furthermore, the possibilities for reducing or slowing down increases in potency are very limited in an illegal or unregulated drug market. However, potency levels constitute a crucial determinant for public health as the main ingredient, delta-9-tetrahydrocannabinol (THC), has been linked to severity of cannabis dependence
^8^, cognitive impairment
^9^, and incidence of psychotic disorders
^10^. Consequently, THC concentrations in legally available products are deemed to be increasingly important by policymakers
^11,
12^. With the legalization of recreational cannabis in Canada and several US American states, it has become mandatory to label all commercially produced cannabis products with their respective THC level (for Canada, see
13,
14).

In addition to the lack of control over potency levels, illegal markets also make it impossible to establish minimum criteria for safety and purity of available products. Analyses of herbal cannabis acquired on the Swiss black market showed that only one in three samples passed the microbiological test for human consumption
^15^. According to one systematic review, microbes, heavy metals, and pesticides constitute the most prevalent contaminants in cannabis products
^16^. While the risks from contaminants to human health have not yet been quantified, case reports highlight that the use of contaminated products may be potentially life-threatening
^17^.

Consequently, legalizing the cannabis market would allow for the control over the rising THC exposure and cannabis-attributable sequelae, and to ensure safety standards of available products are being met. However, there is a multitude of options to realize legal access to cannabis. One option is the creation of so-called ‘cannabis social clubs’, which are established by consumers with the aim of growing and distributing herbal cannabis on a non-for profit basis (e.g., in Uruguay, Spain, Belgium
^18,
19^). More prominently, legal markets in North America have been established by private retailers or government monopolies, while some jurisdictions allow users to grow their own cannabis themselves.

A combination of different modes of access to legal cannabis can be observed in Uruguay, where users may grow their own cannabis, acquire cannabis through membership in a social club or through licensed pharmacies, which get a limited supply of herbal cannabis from government-licensed suppliers
^20,
21^. In fact, a pilot project was proposed in 1997 for a regulated sale of cannabis in pharmacies in a German state
^22^. While this proposal was never implemented due to lack of political support, the ‘pharmacy model’ has several advantages over other private models as pharmacists are trained to test substances with regard to purity and are also more familiar with recognizing substance misuse than are commercial vendors, especially those who are selling product over the Internet. Further, pharmacists are already familiar with dispensing medical marijuana in Germany, and already meet the requirements for dealing with classified substances, such as cannabis.

To inform a cannabis regulation model for Germany, evidence gathered from evaluations of jurisdictions legalizing cannabis in the Americas may serve as a useful base. However, North American cannabis users differ from European users in regard to use modes (e.g. lower co-use of tobacco
^23^, higher use of concentrates
^24,
25^) and patterns (e.g., the stark increase of daily use in the USA
^26^), demanding different requirements for a regulation model in Germany. Further, evidence collected from large-scale natural experiments has its limitations, which may be overcome in small-scale, controlled experiments
^27^. Thus, evaluating tightly regulated cannabis administration models in European jurisdictions is required.

In this study protocol, we outline the proposal for the regulated sale of cannabis to a limited number of users in Berlin, Germany. Responding to calls to make cannabis safer
^28^, this study sets out to reduce harm to recreational users through: a) use of legal cannabis products free from contaminants and pollutants, and b) capping maximum THC-levels and incentivizing the purchase of low-potency cannabis products by aligning retail prices with potency levels and thereby reducing THC exposure among users.

## Protocol

Version: 1 (26 February 2020).

This protocol has been written in accordance with the SPIRIT guidelines
^29^.

### Study design, sample and recruitment

The aims of the study will be evaluated using a quasi-experimental two-group study design, as summarized in
Figure 1. The intervention will constitute an individualized licence to purchase herbal cannabis in selected pharmacies for a duration of 12 months in Berlin, Germany. Control group participants will be recruited in Hamburg, a city comparable to Berlin in terms of sociodemographic indicators (population, deprivation) and user characteristics
^30^.

**Figure 1. f1:**
[figure not shown]
Study flow chart.

Prior to any data collection, study team members will take consent of each participant. A model consent form is available as
*Extended data*
^31^. In both study groups, participants will be asked to complete a questionnaire and provide their usual consumption unit (e.g., joints, mix of tobacco and cannabis to smoke in water pipe, etc.) at both baseline and again after one year (T12). In predetermined intervals, additional questionnaires will be completed by all participants. Further, individual sales data will be collected for intervention group participants, which will be part of the primary outcome analyses.

All participants will be recruited via posters, or through consumer groups and local stakeholders in each city. To incentivize study participation and minimize loss to follow-up, participants will be reimbursed with 25€ upon completion of the questionnaires at each wave. Further, providing details regarding their usual consumption unit will be reimbursed with 15€ (at baseline and at one-year follow-up).

Every resident in the respective control or intervention municipality aged 18 years or above reporting to have used cannabis at least monthly in the past 6 months may participate in the study. Following international recommendations to minimize cannabis use risks
^32^, persons with a familial predisposition to psychotic or substance use disorders, pregnant women, persons in current psychiatric treatment or with a preceding psychotic disorder will be excluded from this study. Further, persons with a prescription to use cannabis for medical purposes will not be eligible to participate as the study focuses on recreational use only.

### Details of the dispensary model

The term dispensary model describes how intervention group participants can acquire cannabis in pharmacies and all measures undertaken to achieve the postulated aim of mitigating use risks. Registered users will be eligible to purchase up to 5 grams of herbal cannabis per transaction and up to 15 grams of herbal cannabis per week. All herbal cannabis will be sold in 1-gram packages, which will be labelled with the concentration of THC and Cannabidiol (CBD,
^33,
34^), and contain further information (e.g., on other constituents, producer, date of production, safety warnings).

Two core measures will deter intervention group participants from using high-potency cannabis varieties. First, we will restrict the sale to varieties containing at most 12% THC, which is just below the median value of 13% identified in herbal cannabis batches seized by the federal police in 2017
^35^. Second, the retail price will be bound to the THC level, with lower potencies being more affordable. Specifically, the variety lowest in THC will be sold at the current black-market price, as determined by the federal police. More potent varieties will be sold at higher prices, with the most potent variety to be sold at 50% above the current black-market price. In this way, purchasing varieties with high THC levels will be disincentivized.

To further mitigate the risks of THC, an upper threshold of the THC/CBD ratio will be established as CBD has been found to attenuate some of the adverse effects of THC (see e.g.
^9,
36^). In the absence of any systematic evidence on the specific risk profile of THC/CBD ratios, an upper threshold of 50:1 was defined based on US data, indicating a worrying ratio increase from 23:1 to 104:1 between 2008 and 2017
^25^.

All herbal cannabis to be sold in the pharmacies will be acquired through the medical supply system
^37^. As of 2019, six out of the 20 varieties available for medical use in Germany
^38^ met the outlined criteria (cap of potency and cap of THC/CBD ratio) to be sold to the intervention group participants in this study. As prescribed for medical cannabis, each batch of herbal cannabis will undergo routine pharmaceutical tests. Further, producers of medical marijuana are legally required to perform systematic tests to detect variations in potency levels and contaminants. In accordance with the requirements of the narcotics law, cannabis stored in the pharmacies will not be accessible to anyone but trained staff. All cannabis products will be stored in a steel cabinet protected by a safety lock, in accordance with the standards prescribed by the German ‘Federal Institute for Drugs and Medical Devices’ (Bundesinstitut für Arzneimittel und Medizinprodukte,
BfArM).

In all participating pharmacies, users will find printed information material on mitigating use risks and will be offered the option of renting devices for vaporizing herbal cannabis. The use of vaporizers can reduce exposure to some hazardous compounds and is hence considered a harm-reducing method
^39^. Further, the vending staff in all participating pharmacies will be trained in the following: legal framework, safer use guidelines (original:
^32^, for a German translation:
^40^), identification of vulnerable users, cooperation with drug counselling and prevention services. If required, study participants will be able to hold conversations with staff in private on the pharmacy premises.

### Primary outcome

Two important aspects will determine the study’s success and will be combined in the primary outcome, measured at baseline and at 12-month follow-up: 1) dominance of legal over illegal consumption, and 2) reduction of THC exposure. The hypothesis for the primary outcome is:

“As compared to baseline, intervention group participants will reduce their use of illegally acquired THC within the past 30 days by at least 50% at 12-month follow-up. Taking into account baseline exposure levels, the total amount of THC consumed among
*intervention* group participants within the past 30 days will fall below the total amount of THC consumed among
*control* group participants within the past 30 days by at least 10% at 12-month follow-up.”

As first aspect, we expect that illicit cannabis use will be largely replaced by consumption of legally acquired products. A shift from an illegal to a legal consumption environment implies that exposure to contaminants and pollutants but also legal consequences (revocation of driver’s licence, imprisonment) will be largely diminished or even completely prevented. As an evaluation of changes in these specific outcomes would require very large sample sizes, and go beyond the scope of this study, we will restrict the first part of the primary outcome to a proxy, i.e., to the percentage of legal cannabis consumption. This will be operationalized as the percentage of an individual’s THC exposure within the past 30 days acquired through purchases in pharmacies.

For the second aspect, we expect to halt the increasing THC exposure among intervention group users. While THC levels in seized and legally available cannabis products are increasing, intervention group participants are expected to reduce their overall THC consumption as compared to control group participants. While THC exposure is the core determinant for cannabis-attributable harm, specific effects on adverse consequences (e.g. on incidence of psychotic disorders) require larger sample sizes which, again, are beyond the scope of this study.

While the first aspect will only be evaluated within the intervention group, the second aspect will require between-group comparisons across a 12-month period. Only if both aspects can be positively evaluated, can an overall success of the study be inferred.

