### Assessment details

For both aspects of the primary outcome, THC exposure within the past 30 days needs to be determined for each respondent by combining the following data sources. First, THC levels per average use occasion will be determined through analyses of usual consumption samples provided at both baseline and after one year (T12). Second, questionnaire data will be used to determine the number of use occasions within the past 30 days, separately for legally and illegally acquired cannabis. Third, and only for the intervention group, sales data will be used to determine THC exposure levels of legally acquired cannabis over a 12-month period.

In summary, for the control group, THC exposure levels within the past 30 days will be determined multiplying THC levels in a usual consumption unit with the number of use occasions reported in the questionnaire. For the intervention group, THC exposure levels will be determined analogously while correcting for the proportion of legally acquired and consumed THC using sales and questionnaire data.

At all waves — T0, T3, T6, and T12 — a set of questionnaires will be administered (see
Table 2). For the primary and secondary outcomes, use characteristics will be assessed using items from the ‘Daily Sessions, Frequency, Age of Onset, and Quantity of Cannabis Use Inventory’ (DFAQ-CU), which will be translated and adapted for this study. All remaining questionnaire data will serve to explain unexpected findings, to control for potential confounders in the statistical analyses, or for the economic evaluation of this study.

**Table 2. T2:** Summary of questionnaire assessment.

Indicator	Questionnaire or item source
Cannabis use characteristics, for primary and secondary outcomes	Items from the DFAQ-CU ^45^
Sociodemographics	Items taken from the WHO Disability Assessment Schedule (WHODAS-II) ^46^
Social situation and participation	Custom-made items
Clinically relevant psychological symptoms	Brief Symptom Inventory (BSI-18) ^47^
Quality of life	EQ5D ^48^
Use of tobacco, alcohol, and other drugs	Custom-made items, AUDIT-C ^49^, use items from EuropASI ^50^
Risky cannabis use/possible cannabis use disorder	CUDIT-R ^51^
Chronic diseases and their treatment	Custom-made items
Utilization of addiction services (counselling, prevention, therapy), for economic evaluation	Custom-made items
Satisfaction and acceptance of the dispensary model	Custom-made items
Adverse events related to using cannabis	Custom-made items

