### Sample size and data analyses

The study outcomes will be analysed according to ‘Intention-to-treat’ (ITT) principles. Specifically, the sample to be analysed is defined as all users who have provided a usual consumption unit within 4 weeks after completing the baseline questionnaire. Over-recruitment will compensate for participants failing to provide a consumption unit within this period. According to ITT principles, only those participants who provided their baseline data, including their usual consumption unit, will be included in the analyses.

To examine between-group differences with a t-test, the required sample size of this study was calculated assuming a power of 80%, a 5% alpha error, and a THC standard deviation equal to one-third of its mean (approximated using Canadian data,
^43^; adding 25% to account for uncertainty). The required sample size was estimated to sum up to n=698 participants (control: n=349; intervention: n=349) for detecting group differences in THC exposure.

Not relevant for sample size considerations, we expect that 20% (control: 30%; intervention: 10%) of all participants of the ITT sample will be lost to T12 follow-up. Subjects dropping out of the study will not be replaced and missing values will be imputed using the ‘Last Observation Carried Forward‘ (LOCF) technique. The critique regarding LOCF imputation methods
^44^ does not apply to our study, as this method will bias the data towards the null hypothesis (assuming no change over time) and therefore representing a conservative imputation approach. The assumptions of LOCF will be examined in sensitivity analyses using advanced multiple imputation techniques.

To evaluate both aspects of the primary outcome, two analyses need to be conducted. First, the THC exposure levels in the past 30 days ascribed to illegal cannabis acquisition within the intervention group needs to be compared between baseline and intervention, with a 50% reduction denoting the minimum threshold for a positive evaluation. Second, a between-group comparison of THC exposure in the past 30 days at T12 adjusting for baseline data will be conducted using a t-test. The dependent variable will be calculated as follows:

$$THC_{T12–adjusted}=\frac{THC_{T12}*100}{THC_{T0}}$$

The actual between-group comparison will be evaluated against the following condition:

$$THC_{T12–adjusted–interventiongroup}<=0.9*THC_{T12–adjusted–control\;group}$$

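### Aspect 1 of the primary outcome rests on a before-after change in Berlin alone, although Hamburg supplies the same measure, so shared background change enters the estimate in either direction

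*Protocol article*

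**What the plan says.** The Primary outcome section of the Protocol article combines two aspects. For the first, the hypothesis is that "intervention group participants will reduce their use of illegally acquired THC within the past 30 days by at least 50% at 12-month follow-up". The section then fixes the comparison: "While the first aspect will only be evaluated within the intervention group, the second aspect will require between-group comparisons across a 12-month period". The two are joined in one success rule: "Only if both aspects can be positively evaluated, can an overall success of the study be inferred".

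Sample size and data analyses repeats the choice as a decision rule. THC exposure "ascribed to illegal cannabis acquisition within the intervention group needs to be compared between baseline and intervention". A fall of one half is the least that counts as a pass. No Hamburg term appears in the rule.

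The Primary outcome section also gives the first aspect another definition, the share of legal consumption: "This will be operationalized as the percentage of an individual’s THC exposure within the past 30 days acquired through purchases in pharmacies".

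On data collection, Study design, sample and recruitment (text after Figure 1) says: "In both study groups, participants will be asked to complete a questionnaire and provide their usual consumption unit", at baseline and after one year. Assessment details states that "for the control group, THC exposure levels within the past 30 days will be determined multiplying THC levels in a usual consumption unit" by the reported number of use occasions, and that occasions are recorded separately for legal and illegal cannabis.

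**The concern.** A before-after change in one group contains the effect of the intervention and everything else that changed over the year: street supply and potency, the effect of repeated questioning, and ordinary drift in use among volunteers. The protocol accepts this for aspect 2, where it expects THC levels to move over time and compares Berlin with Hamburg. It does the same for the secondary outcomes. Aspect 1 covers the same 30-day window over the same year but has no comparator.

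Aspect 1 is half of the success rule. Without a comparator, the 50% threshold can be met partly by a fall that also occurred in Hamburg, or missed because of a rise that occurred in both cities. The change in illegal THC then cannot by itself be attributed to legal access.

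**Working it through.** **No planned figure to reproduce.** The protocol gives no power or sample-size figure for aspect 1. The stated n=698 concerns the between-group comparison of aspect 2.

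**Inputs**
- Pass rule for aspect 1: Berlin ratio B = illegal THC at T12 / illegal THC at T0, with B ≤ 0.50 (Sample size and data analyses).
- Hamburg ratio c = THC at T12 / THC at T0. Not given in the documents; 0.7 to 1.1 is an assumed range.
- Expected loss to T12 follow-up: 30% control, 10% intervention, filled by LOCF (Sample size and data analyses).

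**Step 1: does Hamburg supply the comparator?** Yes. Consumption units and questionnaires are collected there at T0 and T12. Controls have no legal access (Abstract), and people with a medical cannabis prescription are excluded. Hamburg's 30-day THC is therefore in effect illegal THC, and the adjusted variable defined for aspect 2 (T12 × 100 / T0) already expresses its change.

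**Step 2: what does passing mean relative to Hamburg?** Reduction relative to Hamburg = 1 − B/c. The last column is the Berlin ratio that a true 50% effect relative to Hamburg would produce, 0.5 × c.

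| c (assumed) | 1 − 0.50/c | 0.5 × c |
|---|---|---|
| 0.7 | 29% | 0.35 |
| 0.8 | 38% | 0.40 |
| 0.9 | 44% | 0.45 |
| 1.0 | 50% | 0.50 |
| 1.1 | 55% | 0.55 (fails) |

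For example, a true 40% reduction relative to Hamburg with c = 0.8 gives B = 0.6 × 0.8 = 0.48. That is an observed fall of 52%, which passes.

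**Step 3: does aspect 2 protect aspect 1?** Multiply both cities' ratios by a common factor g. The aspect 2 condition, Berlin ≤ 0.9 × Hamburg, becomes g × Berlin ≤ 0.9 × g × Hamburg, and g cancels. The aspect 1 condition becomes g × B ≤ 0.50, and g remains. So aspect 2 does not correct aspect 1.

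**Step 4: is Hamburg's observed ratio trustworthy under LOCF?** Only partly. If the 30% who drop out are carried forward at their baseline value and resemble completers at baseline, the observed ratio is 0.7 × c + 0.3. True ratios of 0.7, 0.8 and 0.9 then appear as 0.79, 0.86 and 0.93. Only 70% of the background change remains visible (for example 0.21/0.30). Berlin is pulled less, because its expected loss is 10%.

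**Step 5: the two definitions of aspect 1.** A participant whose illegal THC falls from 100 to 45 units with no pharmacy purchase shows a 55% reduction and counts towards the 50% rule, yet has a pharmacy share of zero. The definitions can disagree. The share is zero in Hamburg and at baseline by design, so a control comparison adds nothing to it.

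**The case against.** The strongest defence is that the 50% fall is an openly declared absolute target with its own rationale: less exposure to contaminants and to legal consequences for the participants themselves. A purely relative rule would change the question. With Berlin at 0.45 and Hamburg at 0.80, the ratio of ratios is 0.45/0.80 = 0.56, so a 55% fall in illegal THC would fail. This stands, and it is why the absolute target should be kept.

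A reader might infer that the present rule favours the pharmacy model. The documents do not support that. The only background direction they describe is upward (prevalence and potency in the Introduction, THC exposure in Primary outcome), and a rise works against the model. Entry requires only at-least-monthly use over six months, which does not select for high exposure, so a regression-to-the-mean fall is possible but not shown.

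A reader might also infer that a fall shared by both cities could produce overall success by itself, or that the study cannot show displacement at all. Neither follows. Aspect 2 must also be met, and a shared fall cancels there. Legal and illegal occasions are recorded separately and individual sales data are collected, so legal use is observed directly in Berlin.

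Two other defences do not repair the gap. The additional multilevel regression is announced for the primary outcome, but no between-group contrast is stated for aspect 1. Limitations names the lack of randomization, but not the missing comparator. Hamburg is itself a non-randomized control, so an unadjusted ratio of ratios would not be enough.

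**Conclusion.** The point holds as a weakness in attribution that should be corrected. It does not invalidate the 50% target. Over an assumed Hamburg ratio of 0.7 to 1.1, a Berlin ratio that just passes corresponds to a reduction of 29% to 55% relative to Hamburg, and a true 50% effect fails if Hamburg's ratio is 1.1. That the bias can run either way follows from the design; its size and sign depend on a ratio the documents do not give. The conclusion concerns the illegal-THC rule in the Abstract, Primary outcome, and Sample size and data analyses. It does not apply to the pharmacy share, and the presence of two definitions for one aspect needs settling in its own right.

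**What to change.** - Keep the within-Berlin reduction of at least 50% as the absolute target.
- Add to the aspect 1 evaluation a Berlin-versus-Hamburg contrast of the T0-to-T12 change in illegal 30-day THC, adjusted for baseline and the measured confounders, with a confidence interval.
- Repeat the contrast under the multiple imputation already planned, because unequal dropout with LOCF pulls Hamburg's ratio towards 1.
- State that the reduction will be attributed to legal access only if this contrast supports it.
- Reconcile the illegal-THC rule (Abstract, Primary outcome, Sample size and data analyses) with the pharmacy-share definition in Primary outcome: say which one decides aspect 1 and what role the other has.

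The cost is wording and one extra contrast on data already collected in both cities. The contrast will be less precise than the one-group change, and it removes only change that the two cities share.
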